### Study population

Based on the international guidelines that have been recently published, patients qualifying for renal denervation should have been unsuccessful in controlling their blood pressure with lifestyle changes and antihypertensive medications. Patients selected for uRDN with the Paradise System as per routine clinical practice on patient selection for renal denervation can be enrolled in the registry. The goal of the study is to collect real-world data on current clinical practices at each participating site. Full details of the study inclusion and exclusion criteria are shown in Table 1. For prospectively enrolled patients, the uRDN procedure is to be scheduled within 30 days of registry enrollment, while retrospectively enrolled patients need to have undergone uRDN within the previous 6 months.

**Table 1 Tab1:** Inclusion and exclusion criteria

Inclusion criteria
Age ≥ 18 years at time of consent
Candidate for uRDN with the Paradise System based on physician’s assessment
OR
Treated with uRDN using the Paradise System within the 6 months prior to consent
Willing to provide written informed consent (appropriately signed and dated) and agreed to have all study procedures performed

Exclusion criteria
Stented renal artery
Age < 18 years
Pregnancy
Known allergy to contrast medium not amenable to treatment
Renal arteries with diameter < 3 mm and > 8 mm^a^
Renal artery with fibromuscular disease^a^
Renal artery aneurysm or dissection^a^
Renal artery stenosis of any origin > 30%^a^
Iliac/femoral artery stenosis precluding insertion of the Paradise catheter^a^

^a^Determined at time of procedure

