### Assessments and data collection

Follow-up visits are scheduled at 3, 6, and 12 months after the uRDN procedure and every 12 months thereafter. Each visit will include medical review, measurement of office BP, medication name and dose). Ambulatory BP data (mean values, heart rate, standard deviation) obtained during routine clinical practice at study centers (including daytime, nighttime and 24-h BP) will be recorded and assigned to the nearest follow-up visit.

Other data collected during routine clinical practice will also be reviewed as part of patient follow-up, including any of the following: physical parameters including body weight, HR, seated and standing office BP; smoking status during follow-up, socioeconomic, and healthcare resource use parameters; electrocardiogram; non-invasive cardiac imaging; urinalysis including micro/macroalbuminuria; blood chemistry (serum creatinine, electrolytes, blood glucose and HbA1c, blood lipids); non-invasive renal artery imaging; any other cardiovascular procedures and treatments including glucose- and cholesterol-lowering drugs and antiplatelet/anticoagulant use, and the occurrence of any cardiovascular/cerebrovascular event (MI, HF, AF, etc.) and cardiovascular or non-cardiovascular death.

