### Safety

All centers participating in the GPS Registry will use the Paradise uRDN system per their normal practice. Therefore, any device-related adverse events will be reported to the appropriate regulatory authorities through the Recor Medical vigilance reporting process. Underlying diseases/pre-existing conditions will not be reported as adverse events unless there has been a substantial increase in the severity or frequency of the problem that cannot be attributed to natural history during the course of the registry. The assessment of safety includes but is not limited to collecting the following events: incidence of new onset end-stage renal disease (eGFR < 15 mL/min/m^2^ or need for renal replacement therapy), significant decline in renal function, new renal artery stenosis > 70% by CTA/MRA, incidence of renal artery perforation or dissection requiring intervention, incidence of hospitalizations for hypertensive crisis or symptomatic hypotension.

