Hypertensive crisis or symptomatic hypotension
New-onset stroke, transient ischemic attack, cerebrovascular accident
Acute myocardial infraction
Any coronary revascularization
Major vascular complication (e.g., clinically significant groin hematoma, arteriovenous fistula, pseudoaneurysm) requiring surgical repair, interventional procedure, thrombin injection, or blood transfusion)
New renal artery stenosis > 70% confirmed by CTA/MRA
Renal artery perforation or dissection requiring an invasive intervention
New-onset (acute) end-stage renal disease (eGFR < 15 mL/min/m^2^ or need for renal replacement therapy)
Significant decline in renal function, defined as a ≥ 50% increase in serum creatinine (mg/mL)

BP, blood pressure; CTA, computed tomography angiography; eGFR, estimated glomerular filtration rate; MRA, magnetic resonance angiography

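### The only renal artery stenosis endpoint accepts CTA or MRA alone, so a severe stenosis diagnosed and treated at catheter angiography is not counted as a stenosis event

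*Protocol article*

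**What the plan says.** The stenosis event is defined twice in the protocol article. Under Safety it is "new renal artery stenosis > 70% by CTA/MRA"; among the safety assessments in Table 2 (Statistical analysis) it is "New renal artery stenosis > 70% confirmed by CTA/MRA". Both name only CTA and MRA.

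The other renal artery item in Table 2 is "Renal artery perforation or dissection requiring an invasive intervention". The only revascularization item is "Any coronary revascularization".

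Follow-up imaging is not scheduled. Assessments and data collection introduces it with "Other data collected during routine clinical practice will also be reviewed as part of patient follow-up", and the list that follows includes "non-invasive renal artery imaging" and, next to it, further cardiovascular procedures and treatments. The standard-of-care part of Table 2 lists renal artery imaging without the non-invasive limit.

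The Safety section leaves its list open: "The assessment of safety includes but is not limited to collecting the following events". Table 1 excludes "Renal artery stenosis of any origin > 30" per cent, judged at the time of the procedure, and the section on the denervation procedure makes anatomic eligibility depend on angiographic requirements.

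**The concern.** Long-term safety is a stated aim of the registry, and a severe new stenosis in a treated artery is one of the few device-specific late events it names. A patient with suspected stenosis can go directly to catheter angiography and be treated in the same session. With no CTA or MRA on file, that patient does not meet the definition as written. The article accepts procedural angiography as evidence that an artery is suitable for treatment, but does not accept later angiography as evidence that it has become severely narrowed, and gives no reason for the difference.

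The cases lost this way include ones serious enough to be treated. A descriptive, single-arm registry has no comparator in which the same loss would occur, so an undercount goes straight into the published rate.

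**Working it through.** **1. Does any route in the listed endpoints count the case as a stenosis?** Take a new stenosis above 70%, seen at catheter angiography and stented, with no CTA or MRA.

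| Item in the article | Is the case counted as a stenosis? |
|---|---|
| Stenosis, Safety section | No: CTA/MRA only |
| Stenosis, Table 2 | No: confirmation by CTA/MRA only |
| Perforation or dissection, Table 2 | No: different lesion |
| Revascularization, Table 2 | No: coronary only |
| Major vascular complication, Table 2 | Not clearly: its examples are groin hematoma, arteriovenous fistula and pseudoaneurysm |
| Creatinine rise of at least 50%, hypertensive crisis, cardiovascular or hemodynamic hospitalization | Possibly an event, but under another name |
| Cardiovascular procedures (routine data) | Can be recorded, but is not an endpoint |

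So the case can be captured in the database, but it does not enter the stenosis count.

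**2. Direction.** Events that qualify by CTA or MRA are a subset of those that would qualify by CTA, MRA or catheter angiography. Leaving out the third route can therefore only lower the count.

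**3. The plan's own figure.** Sample size states a 95% probability of observing an event with a true rate of 0.1% in 3000 subjects. With P(at least one) = 1 − (1 − p)^n, p = 0.001 and n = 3000: 1 − 0.999^3000 = 0.9503. The figure reproduces. It presumes that every event occurring among the 3000 would be counted.

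**4. Effect of the modality limit.** Let m be the share of severe stenoses confirmed only at catheter angiography. The counted rate is p(1 − m). The article gives no value for m; the values below are assumptions chosen only to show the scale, with p = 0.1%.

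| m (assumed) | Expected count in 3000 | P(at least one counted) |
|---|---|---|
| 0% | 3000 × 0.001 = 3.0 | 95.0% |
| 20% | 3000 × 0.0008 = 2.4 | 1 − 0.9992^3000 = 90.9% |
| 50% | 3000 × 0.0005 = 1.5 | 1 − 0.9995^3000 = 77.7% |

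**5. Why the number imaged is needed as context.** Suppose, as a limiting case, that a stenosis can be detected only in patients who are imaged and that imaging is unrelated to risk. The share imaged is again an assumption. The last column is the exact one-sided 95% upper bound after zero events, 1 − 0.05^(1/n).

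| Share imaged (assumed) | n | P(at least one) at 0.1% | Upper bound, zero events |
|---|---|---|---|
| 100% | 3000 | 95.0% | 0.10% |
| 50% | 1500 | 77.7% | 0.20% |
| 20% | 600 | 45.1% | 0.50% |
| 10% | 300 | 25.9% | 0.99% |

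This is the pessimistic end. If clinicians image mainly those they suspect, a patient who is not imaged still carries some information, and the true position lies between the row for the share imaged and the 100% row.

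**The case against.** The strongest reply is that the case is outside one definition but not lost. The safety list is expressly open, adverse events are collected, device-related events go to vigilance reporting, and cardiovascular procedures are recorded. That stands. A reader might infer that such a patient has no event under any listed endpoint; the documents do not support this, because the same patient may meet the creatinine, hypertensive-crisis or hospitalization item. What the reply does not answer is that being recorded elsewhere is different from being counted as a stenosis.

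A reader might also infer that patients who are never imaged are counted as free of stenosis. The Statistical analysis section says that safety is analysed on the whole study population with frequencies and percentages, but it gives no rule for unimaged patients. The analysis plan, which is not shown, may set one.

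Two further readings fail. The word new does have an implied reference: eligibility excludes stenosis above 30% at the procedure, so a later stenosis above 70% in an eligible artery is new. And nothing in the article shows that the undercount would be worst in patients with chronic kidney disease.

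Finally, a rate among imaged patients would have its own bias. Imaging follows routine practice, so imaged patients are probably selected for suspected disease, and a rate among them may overstate incidence. That stands, and limits what the number imaged can be used for.

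**Conclusion.** The concern holds for the wording of the endpoint. Both definitions restrict the stenosis event to CTA or MRA, and no listed safety item names renal artery revascularization. A severe stenosis diagnosed and treated at catheter angiography without CTA or MRA is therefore not counted as a stenosis event, although it may appear as a procedure or under another item. The bias in the stenosis count is downward only. Its size equals the share of severe stenoses confirmed solely at catheter angiography, which the article does not give and does not allow to be estimated; the shares used above are illustrations.

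The 95% figure under Sample size is arithmetically correct and is not at fault. The point about imaging is a request for context, not a finding that the denominator is wrong. The change should be made, because the definition governs a main device-safety event and is easily corrected.

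**What to change.** - In the Safety section and in Table 2, define the event as a new renal artery stenosis above 70% by CTA, MRA or catheter angiography, or any renal artery revascularization for stenosis.
- In Assessments and data collection, bring the description of renal artery imaging into line with Table 2, which has no non-invasive limit.
- Report the event count over all treated patients and, beside it, the number with any post-procedure renal artery imaging. State that imaged patients are probably selected for suspected disease, so that a rate among them may overstate incidence.

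Cost: minor changes to protocol and case report form wording. Cardiovascular procedures are already collected and no imaging is added. The reported stenosis rate may be slightly higher.

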## Discussion

Hypertension remains the most prevalent cardiovascular risk factor and lowering BP in hypertensive patients reduces the risk of major cardiovascular events [22].

The RADIANCE-HTN SOLO study, in which untreated patients with hypertension were included, demonstrated the BP-lowering effect of uRDN at 2 months; this BP-lowering effect was maintained at 36 months when uRDN patients needed fewer antihypertensive medications than sham patients [23]. The RADIANCE-HTN TRIO trial confirmed the ability of uRDN to lower BP also in patients with resistant hypertension. In addition, observational data from the European multicenter ACHIEVE study confirmed the benefits of uRDN in patients with resistant hypertension [16]. Over 12 months of follow-up, decreases from baseline in mean office and 24-h ambulatory systolic BP were 15 mmHg and 7.5 mmHg, respectively (both *p* < 0.001) [16]. The SPYRAL HTN-OFF MED pivotal trial, in which patients with uncontrolled BP were treated with radiofrequency RDN demonstrated significant reductions in BP in absence of AHM at 3 months. Interestingly, the rate of hypertensive urgencies following RDN was significantly less (9.6%) as compared to sham (17%) between baseline and 3 months [24].

Besides randomized, sham-controlled trials, large-scale registries are particularly relevant for detection of rare events and for collecting information when devices are used in real-world conditions treated across multiple geographies outside of the confines of rigorously conducted clinical trials which increase their internal validity but with strict inclusion/exclusion criteria that lower their external validity or applicability [25]. These registries represent an important source of clinical data to support the long-term safety and effectiveness claims in a broader population, which will include subgroups under-represented in the randomized controlled trials to date. Indeed, the Global Symplicity Registry investigating radiofrequency RDN has provided interesting insights into the BP-lowering efficacy of the procedure out to 3 years [26], the response of patient subgroups with high and very high cardiovascular risk [27] as well as those with and without CKD and the potential impact of the procedure on time in therapeutic range and the subsequent consequences on cardiovascular events [27]. Long-term follow-up after radiofrequency renal denervation has also shown the BP-lowering effect of RDN maintained out to 5 years post procedure in the absence of escalating antihypertensive medications over time [28].

Ambulatory, home, and office BP measurements provide complementary information [25]. While ambulatory and office BP measurements were used in most of the randomized clinical trials and registries, limited information on the impact of RDN on home BP at long-term follow-up is currently available. The GPS Registry will provide the unique opportunity to assess teletransmitted home BP every 3 months with a dedicated telemetric device. Out-of-office home BP measurements are more reproducible than office measurements and are more closely associated with hypertension mediated organ damage (HMOD) and the risk of cardiovascular events and are thus recommended by several hypertension management guidelines [6, 8, 20]. Furthermore, the use of HBPM will facilitate increased data collection in patients over time to see how their BP evolves following uRDN. It will also permit ongoing data collection in the GPS Registry even in the event of further outbreaks of the COVID-19 or other pandemic [29]. As has been shown, one of the biggest limitations of a registry is losing subjects to follow-up. A benefit of collecting home BP is that the data will be automatically uploaded to the cloud, which will enable better long-term follow-up of patients regardless of attendance for office visits and it will allow for the collection of BP between the visits.

## Conclusion

The GPS Registry will collect relevant information on the use of uRDN under real-world conditions to evaluate the safety and effectiveness of this procedure in treating uncontrolled hypertension in a large cohort of patients.

## Data Availability

The datasets will not be publicly available because patient consent in each institute does not allow for such data publication. The corresponding author will respond to inquiries on data analyses.
